#### Both groups

Fifteen minutes after randomisation, women in both groups will complete a short questionnaire on two aspects previously measured just before randomisation, i.e., the perceived pain measured by the VAS and the comfort of their position evaluated by the Likert scale. One hour after randomisation, verification of the fetal head position will be performed, for assessing the primary outcome. Fetal head position will also be recorded at full dilatation of the cervix (before starting pushing efforts). The head position at delivery will also be reported in the data collection forms. Obstetrical and neonatal data will be collected in the medical record.

### Outcome measures

Our primary outcome measure will be fetal head in anterior position one hour after randomisation or at delivery if it happens first.

We have chosen one hour after randomisation rather than at full dilatation of the cervix as the time between randomisation and delivery can be very long. Thus, we estimate that it would be impossible and not ethic to control the position adopted by the participants for such a long time. In addition, one hour of expectant management is a duration that seems acceptable for both women and midwives in the control group, as they may be disappointed to be allocated to the control group. One hour after randomisation, women of both groups may adopt the position of their choice, hands and knees positions included.

Secondary outcomes: evaluation of the comfort of maternal positions; impact of the maternal position on the perceived pain; duration of the first and second stage of labour; mode of delivery according to the fetal head position; perineal status; neonate data (umbilical cord pH and apgar score < 7 at 5 minutes).

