#### Inclusion criteria

The study will be limited to nulliparous and multiparous women during the first stage of labour with a cervical dilatation between 2 to 9 cm, a singleton pregnancy at term (≥ 37 weeks’ gestation), and an OP position diagnosed by ultrasound.

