#### Randomisation

When women give their written consent to participate, a research midwife or the attending midwife will proceed with randomisation through a web-based system provided by the informatics department of the Geneva University Hospitals. Randomisation will be performed using randomly permuted blocks of varying size (4, 6 and 8), stratified by parity (nulliparous/multiparous) and epidural analgesia (yes/no). The ratio for hands and knees versus expectant management is 1:1. After confirming eligibility and consent, the system will return the allocation of the women to the midwife.

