### Interventions

#### Hands and knees position arm

Immediately after randomisation, women allocated in this group will be invited to choose one of the six positions described by [name] (Figure 2). According to this author, all these positions have the same impact on the OP position. The research midwife will present photographs of the six fitted positions (Figure 2) to help the women deciding which position is the best for her. These positions have three important points to be observed: 1) resting on the knees and, if necessary, on the hands; 2) the abdomen must be thrust forward; 3) the back is always stretched. A pillow should be placed between the legs of the woman in labour to limit discomfort. The woman decides if she wants to place her abdomen on a cushion or leave it unsupported. To help the women to take the appropriate position and to be sure that the position is correct, [name] has trained all midwives working in the delivery room of the maternity in the management of the OP position by specific positions of hands and knees. We shall recommend that participants to keep the position as long as they feel comfortable, but a minimum of 10 minutes is required. After this time, they can remain in the hands and knees’ position or change position if they prefer. Time spent in the evaluated position will be recorded in the data collection form.

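### First-stage duration, a secondary outcome, includes labour before randomisation; time from randomisation to full dilatation, adjusted for dilatation at entry, would usually be more precise

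*Protocol article*

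**What the plan says.** The secondary outcomes in the protocol article (Outcome measures) include "duration of the first and second stage of labour". No starting point after randomisation is attached to the first-stage part.

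Eligible are "women during the first stage of labour with a cervical dilatation between 2 to 9 cm" (Inclusion criteria), so every participant has spent part of that stage before allocation. Treatment starts later: "Immediately after randomisation, women allocated in this group will be invited to choose one of the six positions" (Hands and knees position arm).

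Other outcomes are tied to randomisation. The primary outcome is "fetal head in anterior position one hour after randomisation or at delivery if it happens first" (Outcome measures). For pain and comfort: "Fifteen minutes after randomisation, women in both groups will complete a short questionnaire on two aspects previously measured just before randomisation" (Both groups).

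Randomisation is stratified by parity and epidural analgesia, and these are the only variables named for possible adjustment (Randomisation; Statistical analysis). Dilatation at entry is in neither list. Continuous outcomes are to be compared by t-test, or by a non-parametric test if they are not Gaussian.

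**The concern.** Each woman's first-stage duration is the sum of two parts: time before randomisation, which is fixed when she is allocated, and time after it, which is all that hands and knees positioning could shorten. With entry allowed from 2 to 9 cm, the first part may be short in one woman and most of the stage in another. It carries no treatment effect but does carry variance, and the planned analysis has nothing to absorb that variance.

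Two things are at stake. A genuine shortening after randomisation is harder to detect, and any saving given as a percentage is divided by a total that includes untouchable time. Abnormally long labour is one of the complications that the article gives as a reason for the trial (Abstract; Background), so readers will look at this outcome.

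**Working it through.** **The plan's own figure.** The only sample-size figure is for the primary outcome: 10% versus 20%, two-sided 0.05, power 80%, 219 per group (Sample size).
- Uncorrected: n = [1.96·√(2·0.15·0.85) + 0.8416·√(0.10·0.90 + 0.20·0.80)]² / 0.10² = 1.4106² / 0.01 = 198.97, so 199 per group.
- With continuity correction: (198.97/4)·[1 + √(1 + 4/(198.97·0.10))]² = 218.5, so 219 per group and 438 in all.

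This matches the plan and does not bear on duration. The article gives no SD, effect or power for duration.

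**Inputs for duration.** From the article: 219 per arm and two-sided 0.05. Assumed: SD of time from randomisation to full dilatation 3 h; true shortening 0.8 h; pre-randomisation SD 1.5, 3 or 4.5 h; correlation ρ between the two parts, varied. The 3 h and 0.8 h were chosen together so that power starts at about 80%.

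**Formulas.**
- SD of total = √(3² + SD_pre² + 2·ρ·3·SD_pre)
- Power = Φ(0.8 / (SD·√(2/219)) − 1.96), with √(2/219) = 0.0956

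**Counted from randomisation.** 0.8 / (3·0.0956) = 2.79, and Φ(2.79 − 1.96) = 0.80.

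**Total first-stage duration.**

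| SD before randomisation | SD of total, ρ = 0 | Power, ρ = 0 | Power, ρ = −0.3 | Power, ρ = −0.5 |
|---|---|---|---|---|
| 1.5 h | 3.35 h | 70% | 82% | 90% |
| 3 h | 4.24 h | 51% | 65% | 80% |
| 4.5 h | 5.41 h | 34% | 44% | 56% |

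Power is lost only when SD_pre² + 2·ρ·3·SD_pre > 0, that is when ρ > −SD_pre/6. The limits are −0.25, −0.50 and −0.75 for the three rows. A positive ρ makes the loss larger.

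**Does changing the clock alone help?** Assume entry uniform over the first stage, mean total duration 10 h, SD of total S, and a constant 0.8 h effect. Post-randomisation time is then total × (1 − U), with U uniform on 0 to 1, and its variance is (100 + S²)/3 − 25.

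Now adjust for the entry point. If dilatation gave it exactly, the adjustment would remove 100/12 of that variance and leave S²/3. If dilatation tracks the entry point with an error SD of 0.2 of the stage (also assumed), the share removed is (1/12)/(1/12 + 0.04) = 0.676 of 100/12, which is 5.63.

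| S | Total, unadjusted | From randomisation, unadjusted | From randomisation, adjusted, imperfect | From randomisation, adjusted, exact |
|---|---|---|---|---|
| 3 h | SD 3.00, 80% | SD 3.37, 70% | SD 2.39, 94% | SD 1.73, >99% |
| 4 h | SD 4.00, 55% | SD 3.70, 62% | SD 2.83, 84% | SD 2.31, 95% |
| 5 h | SD 5.00, 39% | SD 4.08, 54% | SD 3.32, 71% | SD 2.89, 83% |

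Moving the clock without adjustment loses power in the first row and gains some in the others. Moving it with adjustment beats unadjusted total duration in every row.

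**Percentage effect.** In the same illustration the mean is 10 h in total and 5 h after randomisation. A 0.8 h saving is 8% of the former and 16% of the latter.

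**The case against.** A reader might infer that the comparison is biased. It is not. Randomisation balances pre-randomisation time in expectation, and the difference in mean total duration still estimates the hours saved after allocation. Only precision and the percentage scale suffer.

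A reader might also take the fall to 34% as established. It is one corner of an assumed range. The sign of the correlation is unknown: slow and fast labours push it positive, while entry at different points of a labour of given length pushes it negative. With enough negative correlation the loss disappears or reverses, as the first table shows. No power is claimed for this outcome, which is half of one item in a secondary list.

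Nor do the documents say how the onset of labour is dated, so unreliable recall of onset cannot be part of the argument.

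The strongest objection is that the article is condensed and gives no operational start for the clock, which a fuller document might supply. That lowers confidence somewhat. But the outcome is named, its plain meaning is the whole first stage, and a later document that counted from randomisation would be replacing that outcome. A fair technical objection also stands: post-randomisation time depends on dilatation at entry, so re-clocking alone can do harm.

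**Conclusion.** The point holds as a matter of precision and interpretation. As worded, the first-stage outcome includes time before randomisation that treatment cannot change, and neither stratification nor the named adjustment variables deal with it. The usual consequences are a less precise comparison and a diluted percentage effect.

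The size is conditional on assumed SDs, effect and correlation. It runs from no loss, under sufficiently negative correlation, to a fall from 80% to 34% with a pre-randomisation SD of 4.5 h and zero correlation. The advantage of the adjusted post-randomisation outcome held in every scenario worked here, but those too rest on an assumed 10 h mean, uniform entry and a constant effect.

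This is a worthwhile, inexpensive improvement to a secondary outcome. The primary outcome, pain, comfort and second-stage duration are not touched by it.

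**What to change.** - In Outcome measures, replace first-stage duration with time from randomisation to full cervical dilatation.
- In Statistical analysis, state that this outcome is analysed with adjustment for cervical dilatation at randomisation, together with parity and epidural analgesia. The two changes must be made together.
- Keep total first-stage duration as a descriptive figure, and leave second-stage duration as it is.

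Little new information is needed. Allocation is by "randomisation through a web-based system", and the primary outcome already requires the time of randomisation to be known. Dilatation has to be assessed for eligibility; the data form should hold its value at randomisation. Full dilatation is already an assessment point (Both groups).

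The costs are a regression in place of a t-test and a figure less directly comparable with published first-stage durations. How to count women who never reach full dilatation is a separate question that arises under either definition.

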### Statistical analysis

Data analysis and reporting will be performed according to CONSORT guidelines for randomised controlled trials. A descriptive table of baselines characteristics will be reported for participants for both groups. Primary and secondary outcomes will be analysed on intention-to-treat basis. Sub-group analysis and eventually adjustment for the variables used for stratification (parity and epidural analgesia) will be performed. Means and their standard deviations will be calculated for continuous variables, and the statistical significance of differences between groups will be tested using Student’s *t*-test. Proportions will be compared between groups and differences will be tested using the chi-square test. If the distribution of the variables is not Gaussian, we shall use non-parametric statistical tests. The effect of the intervention will be estimated by the relative risk and its 95% confidence interval and p values to test the significance of the differences will be calculated.

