### Sample size

We calculated that a sample size of 438 women (219 per group) will be needed to obtain a power of 80% with a two-tailed significance of 0.05 to show a statistically significant difference in the incidence of the main outcome measure. We hypothesized that the difference between groups in the proportion of fetuses rotating in anterior position one hour after randomisation will be 10% (10% in the control group versus 20% in the intervention group), a difference that we consider to be clinically significant.

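### Randomisation is stratified by parity and epidural, but the primary test ignores the strata: valid, yet conservative and slightly less powerful if they predict rotation

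*Protocol article*

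**What the plan says.** Under Randomisation, the protocol article allocates women in permuted blocks, "stratified by parity (nulliparous/multiparous) and epidural analgesia (yes/no". That gives four strata, and allocation is balanced: "The ratio for hands and knees versus expectant management is 1:1".

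The primary endpoint is binary (Outcome measures): "Our primary outcome measure will be fetal head in anterior position one hour after randomisation or at delivery if it happens first". For such endpoints the Statistical analysis section says "Proportions will be compared between groups and differences will be tested using the chi-square test" and "The effect of the intervention will be estimated by the relative risk and its 95% confidence interval". Neither the test nor the estimate is described as stratified or adjusted.

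The only mention of the strata in the analysis is "Sub-group analysis and eventually adjustment for the variables used for stratification (parity and epidural analgesia) will be performed". No model is named. The word *eventually* can be read as 'in the end' or as 'possibly', and the sentence does not say how the adjusted result stands to the unadjusted one. The Sample size section asks for 438 women (219 per group) to give "a power of 80% with a two-tailed significance of 0.05" for 10% versus 20%.

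**The concern.** Blocking within strata makes the arms nearly equal on parity and epidural status. If those factors predict whether the head rotates, the difference between arms varies less from trial to trial than a simple two-group formula assumes. An unstratified chi-square does not use this. Its standard error is too large, its true type I error falls below 5%, and it rejects less often than it could when the intervention works.

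What is at stake is efficiency and one clearly named primary analysis, not validity. The design already bears the effort of stratifying, and the analysis as written does not collect the benefit.

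**Working it through.** **1. The plan's own figure.** Inputs from Sample size: 10% and 20%, two-sided 0.05, power 80%. The mean proportion is 0.15.

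- Without continuity correction: n = [1.96·√(2·0.15·0.85) + 0.8416·√(0.10·0.90 + 0.20·0.80)]² / 0.10² = (0.9898 + 0.4208)² / 0.01 = 198.97, so 199 per group.
- With continuity correction: n' = (198.97/4)·[1 + √(1 + 4/(198.97·0.10))]² = 218.5, so 219 per group. This matches the stated figure exactly.
- Power of an uncorrected chi-square at 219 per group: Φ[(0.10·√219 − 0.9898)/0.5] = Φ(0.980) = 0.837.

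The sample size is therefore for an unstratified comparison, and it holds a small reserve if the test is run without correction.

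**2. Assumptions the documents do not supply.** Shares: 65% nulliparous, with epidural in 75% of nulliparous and 60% of multiparous women. The stratum weights are then 0.4875 (nulliparous, epidural), 0.1625 (nulliparous, none), 0.21 (multiparous, epidural) and 0.14 (multiparous, none). Each factor is given the same odds ratio (OR) for rotation, and the overall rate without an effect is held at 10%. Control rates in that stratum order:

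- OR 2: 6.0%, 11.3%, 11.3%, 20.4%
- OR 3: 4.0%, 11.2%, 11.2%, 27.5%
- OR 5: 2.2%, 10.3%, 10.3%, 36.4%

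**3. Direct check of the standard error.** With exact balance within strata and no treatment effect, the chi-square uses the variance p(1−p), about 0.090. The variance that applies is the weighted mean of p_k(1−p_k) over the strata.

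- OR 2: 0.0275 + 0.0163 + 0.0210 + 0.0227 = 0.0876. The standard error is overstated by √(0.0899/0.0876) = 1.013. Type I error = 2·[1 − Φ(1.96·1.013)] = 0.047.
- OR 3: 0.0187 + 0.0162 + 0.0209 + 0.0279 = 0.0837. Ratio √(0.0898/0.0837) = 1.036. Type I error 0.042.
- OR 5: 0.0105 + 0.0150 + 0.0194 + 0.0324 = 0.0773. Ratio √(0.0900/0.0773) = 1.079. Type I error 0.034.

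**4. Simulation.** 438 women, near-balance within the four strata, 200,000 trials per scenario, 10% versus 20% for power. Both tests are uncorrected; CMH is Cochran-Mantel-Haenszel.

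| OR per factor | Type I error, chi-square | Type I error, CMH | Power, chi-square | Power, CMH |
|---|---|---|---|---|
| 1 | 0.050 | 0.049 | 84.3% | 84.3% |
| 1.5 | 0.049 | 0.049 | 84.2% | 84.6% |
| 2 | 0.048 | 0.050 | 84.5% | 85.5% |
| 3 | 0.043 | 0.049 | 85.1% | 87.4% |
| 5 | 0.037 | 0.049 | 86.1% | 90.5% |

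A second, separate simulation at ORs 2, 3 and 5 gave chi-square type I errors of 0.048, 0.043 and 0.034, and CMH gains of about 0.7, 1.9 and 3.7 power points. The first gives about 1.0, 2.3 and 4.4. The two agree on a loss of about 1 to 4 points.

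If the chi-square is continuity-corrected, which the plan leaves open, its power in the first simulation runs from 80.7% to 82.5%, still above 80%.

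**5. Testing both ways.** In the first simulation, declaring success if either uncorrected test is significant gives a type I error of at most about 0.052.

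**The case against.** The strongest reply is that little is lost. The planned test errs in the safe direction and keeps at least 84% power uncorrected, above the planned 80%. For ORs up to 2 the loss is about 1 point or less. This stands, and it limits the point to efficiency and clarity.

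The size also rests on a premise the protocol does not supply. Its Background links epidural analgesia and parity to the occurrence of a posterior position. The primary outcome is rotation within an hour among women whose fetus is already posterior. The article does not say that either factor predicts that, nor why the strata were chosen. This stands too, so the effect must be given as a range that starts at zero.

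A third reply is that the choice of estimator can be left to an analysis plan that is not shown. This stands only in part. The article names a test and an effect measure, and describes the adjustment in non-committal words, so it fixes the point loosely instead of leaving it open.

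A reader might infer more than the text bears:

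- *That the headline result can be picked once the data are seen.* The wording is loose, but a fair reading makes the unadjusted comparison the main one, and taking the better of the two tests moves type I error only to about 0.052.
- *That subgroup claims will mislead.* The article does not describe the subgroup method, so separate p values within subgroups cannot be assumed. An interaction test is detail an analysis plan may hold.
- *That the relative risk is the wrong measure, because the 10-point gap is* "a difference that we consider to be clinically significant". At a 10% control rate, 10 points is a relative risk of 2, and the proportions in each arm are to be compared anyway. There is no contradiction.

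**Conclusion.** The mismatch is real and modest. The trial stratifies its randomisation, but the stated primary test and relative risk do not use the strata, and adjustment is left as *eventually*. If parity and epidural status predict rotation with an OR of 2 to 5 each, the test runs at a type I error of about 0.048 down to 0.034 and loses about 1 to 4 power points against a stratified test. If they do not predict rotation, nothing is lost.

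The direction follows from the design. The size depends on the assumed stratum shares and ORs, for which the documents give no figures. Nothing here supports calling the planned test invalid or the trial underpowered. The change is worth making because in these scenarios the stratified test costs essentially no power and can gain some.

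**What to change.** In Statistical analysis, replace the loose adjustment wording with one named primary analysis: a Cochran-Mantel-Haenszel test over the four parity-by-epidural strata, with the Mantel-Haenszel relative risk and its 95% confidence interval. Use parity and epidural status as entered at randomisation, so that an epidural placed later does not move a woman between strata. Name the unadjusted chi-square and unadjusted relative risk as supportive.

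The cost is a few lines of text, best settled before outcome data are examined. The stratum variables are already in the randomisation system, and neither the sample size nor data collection changes.

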### Sample size

We calculated that a sample size of 438 women (219 per group) will be needed to obtain a power of 80% with a two-tailed significance of 0.05 to show a statistically significant difference in the incidence of the main outcome measure. We hypothesized that the difference between groups in the proportion of fetuses rotating in anterior position one hour after randomisation will be 10% (10% in the control group versus 20% in the intervention group), a difference that we consider to be clinically significant.

### Feasibility

Approximately 15% of women will present a fetal OP position during the first stage of labour and this will concern 600 women per year at our maternity. By our previous experience, we estimate that around 50% of potentially eligible women will be screened (difficulty of the diagnosis during labour) and/or informed (depending on workload in the delivery rooms, emergencies). Thus, we estimate that study entry will be proposed to around 300 eligible women per year. We plan to enrol 150 women per year (12–13 per month). The required sample size could then be reached in around 35 months.

### Timetable

Total 42 months: commencing February 2010 with estimated completion June 2014.

1–2 months: regulatory approvals, preparation of the trial.

3–38 months: recruitment, intervention, data collection.

39–42 months: data analysis, reporting, peer review publications, conference presentations.

### Ethical aspects and safety considerations

The study protocol has been accepted by the institutional ethics committee of the Geneva University Hospitals (n° CER10-182). The safety of mothers and fetuses will be closely monitored as part of this study and a monitoring committee has been formed. Before enrolment, a research assistant or midwife will inform the women of the study. An information form will be available. A short period of reflection will be offered to decide upon participation due to an eventual emergency situation (imminent delivery). Women may withdraw consent at any time without negative consequences on the quality of care or staff attitude. Data will be treated on a confidential basis. Participants will be identified in the computerised database by a number that will be attributed at the same time as inclusion in the study. Study results will be reported in an anonymous form to protect the identity of participants.

